## SUMMARY

Interest of dementia tracking in nursing home: contribution of multidisciplinary team meeting (MDTM) in Alzheimer's disease and related diseases- IDEM Study

### JUSTIFICATION

Access to the diagnosis of Alzheimer's disease and other dementias remains a problem in France especially after the age of 80 (Expertise INSERM 2007). Epidemiological data currently available in France report that in the general population, only half of patients with Alzheimer's disease are diagnosed (Gallez C., 2005).

The absence of a diagnosis of dementia at an early stage reduces the chances of optimal patient management. A consequence of the non-diagnosis of dementia is the inappropriate use of care services, including increased recourse to emergency hospitalization (Gordon et al., 1991; Kayser-Jones et al., 1989; Kerr et al., 1991).

Although the value of screening in the general population is not conceivable in the absence of curative treatment of dementia, the question of systematic detection of dementia cases arises in nursing homes (NH) because of the high frequency of dementia (50 to 70% depending on the case) and its under-diagnosis. While, the benefit of appropriate care is recognized even at an advanced stage of the disease (Expertise INSERM 2007), no study to our knowledge has been conducted on the interest of a systematic detection of dementia in nursing homes.

### OBJECTIVES

The objective of the IDEM study is to evaluate the impact of a systematic screening of cases of dementia performed in the framework of MDTM (Multidisciplinary Team Meeting) in nursing home (NH).

|                    |                                                                   |                                                                                                            |
|--------------------|-------------------------------------------------------------------|------------------------------------------------------------------------------------------------------------|
| Principal analysis | Statistical Analysis Plan (SAP)-IDEM Study 0910701
Version 1.0 | [figure not shown]
Hôpitaux de Toulouse |
|                    |                                                                   | 07/22/2016                                                                                                 |

The interest of this approach is evaluated on the rate of emergency department (ED) transfers at one year. Our hypothesis is that a systematic identification of dementia cases in EHPAD reduces the rate of ED transfers.

The secondary objectives are to determine the impact of systematic screening of dementia on the quantity and type of drug prescriptions (neuroleptics, benzodiazepines, antidepressants, hypnotics, anxiolytics, thymo-regulators, anti-cholinesterases, memantine) and non-drug treatments (physiotherapy, occupational therapy, psychological counseling, dietetics, speech therapy), the appropriateness or inappropriateness of hospitalizations (including emergencies), the prevalence of psycho-behavioral disorders, the residents' process of entry into the dependency, the quality of life of residents, the burden of the NH staff, the advanced care planning measures (advance directives ...) and the overall cost of care.

#### DIAGRAM OF THE STUDY

Multicenter, randomized by NH (1:1) comparing two-parallel groups:

- an intervention group, corresponding to NH that set up MDTM to identify patients with dementia and to discuss an appropriate care plan,
- and a control group, corresponding to NH that continued their usual practice.

#### INCLUSION CRITERIA

During the inclusion period, all the residents of participating NH who meet the study criteria are included in the study: subjects aged 60 years or older, without diagnosed or documented dementia, not bedridden [Groupe Iso-Ressource (GIR) >1), living in the NH for at least one month at inclusion, with a life expectancy of more than one year and without any disease likely to jeopardize his/her participation in the study.

#### RESEARCH PROCESSES

The project is based on the REHPA network (Research in NH), set up in 2008 by our team and regrouping 240 NH with the aim of setting up clinical research projects specifically adapted to NH population. The cluster randomization takes into account some characteristics of NH related to the type of institution and the type of residents.

After being trained, the coordinating physicians practicing in the NH of the intervention group carry out a comprehensive geriatric assessment for each participating resident. The results of the various

|                    |                                                                   |                                                                                                                   |
|--------------------|-------------------------------------------------------------------|-------------------------------------------------------------------------------------------------------------------|
| Principal analysis | Statistical Analysis Plan (SAP)-IDEM Study 0910701
Version 1.0 | [figure not shown]
Hôpitaux de Toulouse |
|                    |                                                                   | 07/22/2016                                                                                                        |

tests are discussed between the coordinating physician and an expert from a nearby “memory resource and research center (MRRC)” or a “memory clinic (MC)” during a MDTM on Alzheimer's disease and related diseases.

Information on hospitalizations, drug and non-drug prescriptions, the appropriateness of hospitalization, the prevalence of psycho-behavioral disorders, residents' dependence and quality of life, the burden of the NH staff, the planning of advance directives and the overall cost of care are collected during follow-up. These monitoring data are collected by an ARC via a secure website (REHPA web page), or if necessary by mail or phone calls. The overall cost of care is provided by the French National Health Insurance Fund.

#### **CALCULATION OF THE NUMBER OF SUBJECTS**

The number of subjects needed to meet our main objective was calculated by hypothesizing a bilateral test with an alpha risk of 5% and a beta risk of 20% (80% power). Based on previous data, we estimated the incidence of ED admissions of 24% at 12 months in the control group. To detect a 30% reduction of the rate of transfers to ED in the intervention group, with a two-tailed test and an  $\alpha$  risk of 5% and 80% power, 1000 subjects were required in each group, taking into account an intraclass correlation coefficient (ICC) at 0.02, 20% of attrition rate and the inflation factor related to contamination between groups of 5 to 10%, during 12-month trial.

#### **INCLUSION AND PATIENTS' FOLLOW-UP**

After a 3-month preselection period to identify the NH residents meeting the study criteria, the preselected residents in both groups have an inclusion visit in the NH realized by the coordinating physician. Each NH include all of its residents in a time interval of two months. Sociodemographic and medical data are collected in both groups. The residents in the intervention group also undergo a comprehensive geriatric assessment. The included residents are followed for 18 months. At the end of follow-up, all the residents in both groups undergo a final visit in the NH performed by the coordinating physician including a simplified comprehensive geriatric assessment.

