### 3.3 Calculation of the number of subjects

The number of subjects required to meet our main objective was calculated by assuming a bilateral test with an alpha risk of 5% and a beta risk of 20% (80% power). On the basis of REHPA survey data (Rolland Y et al. 2009), 13.5% of all residents reported in the REHPA survey were admitted to hospital services in 3 months, an estimate of 54% in 1 year. By limiting the population of the REHPA survey to subjects with the inclusion criteria defined in IDEM, 12% were admitted to hospital services in 3 months, an estimate of 48% at 1 year. According to the same survey, of the 48% of all hospitalizations, half were via ED. Indeed, we can estimate an incidence of ED transfers of 24% at 1 year in the non-intervention group. Assuming a 30% reduction in the ED transfer rate in the intervention group, the 12-month ED transfer rate will be 16.8%. 516 subjects are needed in groups, taking into account the cluster effect with an ICC set at 0.02 of an attrition rate of 20% (average known % of deaths per year from REHPA data), the minimum number of subjects per group varies from 950 to 1050 depending on the inflation factor linked to the contamination between the groups, which has been varied from 5 to 10%.

|                    |                                                                   |                                                                                                            |
|--------------------|-------------------------------------------------------------------|------------------------------------------------------------------------------------------------------------|
| Principal analysis | Statistical Analysis Plan (SAP)-IDEM Study 0910701
Version 1.0 | [figure not shown]
Hôpitaux de Toulouse |
|                    |                                                                   | 07/22/2016                                                                                                 |

In total, 1,000 residents per group or 2,000 residents must be included. Taking into account an inclusion number of 30 residents on average per NH, 35 institutions per arm are necessary. Given the potential of 240 NH of REHPA network, this number of institution is realistic to achieve. In total 89 nursing homes have volunteered.

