## 5 STUDY POPULATIONS

### 5.1 Intention to treat population (ITT)

The ITT population will consist of all subjects included in the study who have at least 1 month of follow-up. That is, all residents of the randomized NH centers who performed the inclusion visit and who did not leave the study within one month of the start of the follow-up (i.e. the end of the inclusion period in the center).

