## 6.2 Complementary analyzes of the primary endpoint

First, a second mixed logistic regression model will be used to study the effect of the intervention on the risk of admission to the ED in the first year, taking into account potential confounders of age, co-morbidities (Charlson), dependency (GIR score), antecedents of psychiatric pathologies and the presence of cognitive decline at inclusion. The effect of the intervention will be tested with a risk of 5% (exploratory test).

Then, in order to consider the differences in the duration of follow-up caused by the deaths and the anticipated stopping of study, other complementary analyzes will be conducted on the primary endpoint.

- Incidence rates defined as the number of emergency room admissions per 100 person-years (i.e. 100 persons followed exactly 1 year in NH) will be calculated for each NH and a statistical test will be performed to determine if the difference between the incidence rates in both groups is significant (exploratory test at 5%). To calculate incidence rates, the at-risk follow-up time for each subject will first be calculated as the time in years between the start date of follow-up (i.e. end date of inclusions in the center) and the date of point (i.e. start date of follow-up plus 1 year) or the date of premature dropout of the study for the subjects who stopped the study before 1 year of follow-up MINUS possible durations of hospitalization (i.e. the subjects are no longer at risk of transfer to the ED

|                    |                                                                   |                                                                                                            |
|--------------------|-------------------------------------------------------------------|------------------------------------------------------------------------------------------------------------|
| Principal analysis | Statistical Analysis Plan (SAP)-IDEM Study 0910701
Version 1.0 | [figure not shown]
Hôpitaux de Toulouse |
|                    |                                                                   | 07/22/2016                                                                                                 |

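### Residents enter through the home's own physician at a visit that differs by arm, yet the only confirmatory test has no resident-level covariates and the adjusted model is only exploratory

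*SAP*

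**What the plan says.** **Design.** The summary describes the trial as "Multicenter, randomized by NH (1:1) comparing two-parallel groups". After a 3-month preselection period, "the preselected residents in both groups have an inclusion visit in the NH realized by the coordinating physician" (Summary, Inclusion and patients' follow-up).

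**Content of the visit.** Sections 6.5.3 and the same summary paragraph place the comprehensive geriatric assessment (CGA) at the inclusion visit in the intervention group alone. Under Research processes, the physicians who carry it out are trained first. Note 1 to the staff-burden endpoint in 4.2 shows that some homes held a second wave of inclusion.

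**Eligibility.** Every resident of a participating home who meets the criteria is to be included. Those criteria end "with a life expectancy of more than one year and without any disease likely to jeopardize his/her participation in the study" (Summary, Inclusion criteria).

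**Analysis set.** Section 5.1 defines ITT as "all residents of the randomized NH centers who performed the inclusion visit", subject also to at least one month of follow-up.

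**Models.** The confirmatory mixed logistic model in 6.1 has randomisation group as fixed effect and centre as random effect, and nothing else. Section 6.2 plans a second model "taking into account potential confounders of age, co-morbidities (Charlson), dependency (GIR score"), psychiatric history and cognitive decline at inclusion, and labels its test exploratory.

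**Non-included residents.** Section 6.5.2 describes their number and the reasons, and 6.5.1 makes descriptions by randomisation group the general rule.

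**The concern.** Randomising homes balances homes in expectation. It balances residents only if entry does not depend on the arm. Here entry rests partly on a physician's view of life expectancy and of disease that could compromise participation. Both bear on frailty, and so plausibly on the risk of an ED transfer. If that view is formed with the arm known, the two samples may differ in baseline risk for reasons unrelated to the multidisciplinary meeting.

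The random centre effect in 6.1 allows for correlation within homes. It does nothing about a systematic difference in case mix between arms. The 5% claim therefore rests on the model with no means of correcting such a difference, while the model that can correct part of it has no confirmatory standing.

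The SAP also leaves open what is concluded if the two models disagree. That gap matters more because section 2 says the analyses will not be blind. Section 6.1 further relies on follow-up times being similar in the two groups, which selection on judged life expectancy could disturb.

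**Working it through.** **1. The plan's own figures.** Section 3.3 assumes a "bilateral test with an alpha risk of 5% and a beta risk of 20% (80% power"), "an incidence of ED transfers of 24% at 1 year in the non-intervention group" and a 30% reduction: 0.24 × 0.70 = 16.8%, a difference of 7.2 points. The two-proportion formula with continuity correction gives 518 per group against the stated 516. With 30 residents per home, 20% attrition and ICC 0.02, the design effect on the 24 retained is 1 + 23 × 0.02 = 1.46. Then 516 × 1.46 / 0.8 = 942, and × 1.05 to 1.10 gives 989 to 1,036, inside the stated 950 to 1,050. Nothing here disputes the sample size.

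**2. When is the arm known?**
- The SAP gives no randomisation date, and preselection may have come before randomisation.
- The inclusion visit is arm-specific, and in intervention homes the physician is trained beforehand. The arm is therefore probably known at acceptance.
- A second wave can only follow a first wave already run under the home's arm. There the arm is certainly known.

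**3. What an imbalance would do to the confirmatory test (illustration).** Inputs from the SAP: 1,000 per arm, 30 per home, ICC 0.02, 24% control risk. Early leavers stay in the 6.1 analysis, so all 1,000 are counted. Design effect = 1 + 29 × 0.02 = 1.58; effective n = 1,000 / 1.58 = 633 per arm. A two-proportion z-test stands in for the mixed model. The size of the imbalance is assumed.

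Rejection probability with no true effect: Φ((d − 1.96·SE₀)/SE₁) + Φ((−d − 1.96·SE₀)/SE₁), where d is the imbalance in risk and SE₀ and SE₁ are the pooled and unpooled standard errors. For d = 0.02 (24% v 22%), both standard errors are about 0.0237.

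| Imbalance in baseline ED risk | Two-sided type I error |
|---|---|
| 0 | 5% |
| 1 point | 7% |
| 2 points | 13.5% |
| 3 points | 25% |
| 4 points | 40% |

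In the other direction, if the 7.2-point effect is real and the intervention sample starts 2 points higher, power falls from about 89% to 62%.

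**4. How much selection produces such an imbalance?** All inputs are assumed: a share s of eligible residents is frail with RR times the ED risk of the others, and one arm passes over a fraction x of them while the other passes over none.
- Non-frail risk b = 0.24 / (1 + (RR − 1)s)
- Frail share left in the selecting arm s₂ = s(1 − x) / (1 − sx)
- Risk in the selecting arm = b(1 + (RR − 1)s₂)

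| s, RR, x | b | s₂ | Risk v 24% | Relative shift | Type I error |
|---|---|---|---|---|---|
| 0.10, 1.5, 0.25 | 0.229 | 0.077 | 23.7% | 1.1% | 5.1% |
| 0.20, 1.75, 0.375 | 0.209 | 0.135 | 23.0% | 4.2% | 7% |
| 0.30, 2, 0.50 | 0.185 | 0.176 | 21.7% | 9.5% | 16% |

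The formula does not depend on which arm selects. If control homes were the ones passing over frail residents, the intervention would look worse by the same amounts.

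**The case against.** Enrolment is meant to be exhaustive: all eligible residents enter, each home within two months. Passing over a quarter to a half of frail eligible residents, as step 4 assumes, would breach that rule. Preselection, where the criteria are first applied, may have come before randomisation. An unadjusted primary test with a prespecified adjusted companion is a conventional choice. The adjusted model already exists, and non-inclusion reasons are already described by arm. Replacing a confirmatory model late, with unblinded analysts, has a credibility cost of its own. Adjustment also cannot reach what a physician senses but does not record.

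Much of this stands. The exhaustive rule should limit selection, but it does not settle matters when eligibility itself turns on judgement. Describing non-inclusions can reveal selection but does not correct it. The convention of an unadjusted primary test is most comfortable when individuals are randomised; it is less so when residents are accepted after the arm is probably evident. The credibility cost is real, and is the reason to make and record the change before database freeze.

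A reader might infer that intervention physicians avoided frail residents because the assessment was burdensome, and that the trial is therefore biased towards the intervention. The SAP does not support this. It reports no resident passed over, calls the assessment simplified (3.1), and gives control homes an inclusion visit with its own data collection. Physicians offered expert advice might equally favour complex residents.

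**Conclusion.** The point holds as a weakness in how the confirmatory analysis is fixed, and is worth correcting. Residents are included by the home's physician at an arm-specific visit, on criteria that partly need judgement, and the only confirmatory test ignores the resident-level factors that the SAP itself calls potential confounders. No rule covers discordant results.

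Neither the direction nor the size of any imbalance can be derived from the SAP. Under the assumed inputs the spurious shift is 0.3 to 2.3 points against the 7.2-point target, with type I error of about 5.1% to 16%; mid-range inputs give about 1 point and 7%. These figures show how sensitive the test is. They do not estimate bias in this trial, and they do not show that selection occurred.

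**What to change.** Before database freeze:

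- **6.1 and 6.2.** Make the 6.2 mixed logistic model the confirmatory analysis, with age, Charlson, GIR, psychiatric history and hospitalisations in the last 3 months as covariates. Section 6.5.3 describes age, Charlson, GIR and recent hospitalisations in both groups. It does not list psychiatric history separately, so confirm that it is recorded alike in both arms.
- **Cognitive decline.** Keep it only if it is the history item that 6.5.3 lists for both groups, recorded the same way in each, and not a result of the CGA.
- **Supporting analysis.** Keep the present 6.1 model as the unadjusted supporting result. Naming one model as confirmatory also settles which one carries the conclusion if they differ.
- **Section 7.** Add a simple rule for missing baseline covariates, so that no ITT resident drops out under the general no-imputation statement.
- **6.5.2.** Add, by arm, the proportion of preselected residents who were included. Reasons for non-inclusion by arm are already planned.
- **Section 2.** Record the change.

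The cost is SAP wording and slightly more analysis work on data the plan already uses. Selection on unmeasured frailty remains, so the inclusion proportions by arm should be read alongside the adjusted result.

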#### **EXPECTED OUTCOMES**

The identification of residents with dementia in NH appears to be a relevant means of optimizing the care of the resident and, in particular, reducing the need for transfers to the ED. The opinion given by a MDTM on Alzheimer's disease and related diseases (plan of care, medication, non-pharmacological

|                    |                                                                   |                                                                                                            |
|--------------------|-------------------------------------------------------------------|------------------------------------------------------------------------------------------------------------|
| Principal analysis | Statistical Analysis Plan (SAP)-IDEM Study 0910701
Version 1.0 | [figure not shown]
Hôpitaux de Toulouse |
|                    |                                                                   | 07/22/2016                                                                                                 |

approaches, advances directives...) would prevent certain frequent situations during dementia leading to hospitalizations.

The demonstration of the interest of a MDTM in the systematic detection of dementia in NH could lead to a generalization of this type of procedure at the national and international level.

**HISTORY OF THE DOCUMENT**

|                    |                                                                   |                                                                                    |
|--------------------|-------------------------------------------------------------------|------------------------------------------------------------------------------------|
| Principal analysis | Statistical Analysis Plan (SAP)-IDEM Study 0910701
Version 1.0 | [figure not shown] |
|                    |                                                                   | 07/22/2016                                                                         |

| VERSION | DATE       | DESCRIPTION DES MODIFICATIONS |
|---------|------------|-------------------------------|
| V1.0    | 07/22/2016 | First validated version       |

